
#### Loneliness and social connectedness

Changes in loneliness and social connectedness will be assessed pre-post intervention and during the intervention through an EMA approach. Several studies have found an effect of mindfulness training on loneliness reduction [102–104]. In the context of performing daily ‘Affect Dyads’ in the ReSource project Kok and Singer [69] observed that participants after a given 10-minutes partner exercise indicated that they felt closer to the partner than before. Interestingly, they also showed that subjective connectedness even increased weekly before each Dyad and even if coupled with a new partner still unfamiliar to yourself. Similarly, over the 13 weeks of training of a module, the degree of personal disclosure, that is what participants were willing to share with the other partner, increased steadily. Thus, a sense of shared humanity and connectedness emerged throughout this socio-emotional training practices. Therefore, we will also assess the social connectedness to the respective dyad partner before and after the daily dyad as well as the degree of personal disclosure that was shown during the dyad. We also expect changes in thought patterns [105], affective states [106] and daily loneliness [107] before and after the dyad. Furthermore, we will ask participants on a weekly basis about other variables related to social connectedness, such as the frequency and quality of their social interactions [108], the sense of belonging [109], common humanity [110], fear of compassion [111] and the social support received in stressful situations [112]. We expect that the socio-emotional training will be more efficient than the mindfulness-based intervention in reducing loneliness and increasing social connectedness. We will assess changes in the above postulated mechanistic variables suggested to mediate the reduction in loneliness in the socio-emotional training.

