#### Stress

We will examine changes in stress before and after the intervention. Mindfulness-based trainings, such as the MBSR program, can significantly reduce stress in healthy individuals [47, 80, 81]. Similarly, socio-emotional trainings have been shown to reduce perceived stress as well as impact hormonal stress markers such as cortisol. In the ReSource project [67], the effects of mindfulness-based and socio-emotional and socio-cognitive trainings (Presence, Affect, Perspective modules) on social stress reduction measured in cortisol levels during the experience of an acute stressor (the Trier Social Stress Task; TSST) were compared, and only the socio-emotional and socio-cognitive training modules which included the daily 10-minutes partner-based dyad exercises showed reliable effects of stress reduction on the hormonal level [68, 76]. Possible underlying mechanisms of all these observed changes are purported to be a social stress buffering effect of learning through the daily dyads with other people to listen and be listened in a non-judgemental manner and to befriend yourself with your own and others vulnerability by practicing acceptance and self-compassion. Further, changes in use of emotion regulation strategies such as acceptance have been proposed [72, 82]. Other possible mechanisms like an increase in interoceptive awareness [83–86], frequency and quality of social interaction [87], common humanity [88, 89], psychological flexibility [90], control over emotions [91], mindfulness [92] and social support [93] as well as a decrease in rumination [94], worry [95] and fear of compassion [96] will be assessed in weekly questionnaires. Other mechanisms that are expected to have an impact on stress reduction through socio-emotional mental training are increased social connectedness and personal disclosure through daily interpersonal practice with another person [69], a decrease in loneliness [97, 98] and changes in current thought patterns [99, 100] and affective states [101]. Those possible mediators will be assessed daily before and after the socio-emotional training intervention to analyze changes and their relation to the expected decrease in stress. In the present study we expect that individuals who undergo the two training interventions will show a decrease in subjectively perceived stress. However, we expect differential changes between the intervention groups in cortisol social stress reactivity after a TSST, and diurnal cortisol stress measured by the cortisol awakening response (CAR) during two consecutive week days in the life of the participants. More specifically, and based on previous research [76], we expect that the socio-emotional Dyad-based intervention as compared to the mindfulness-based intervention will be most efficient in decreasing stress on the hormonal cortisol levels, both for the CAR and acute stress reactivity after a social stressor.

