#### Pre-post questionnaires

We will assess change from baseline to 10 weeks after the intervention using the following validated questionnaires which will be administered at pre-test, post-test and post-test 2: Perceived Stress Scale-10 (PSS-10; [196]), UCLA Loneliness Scale [197]), Beck Depression Inventory-II (BDI-II; [113]), Connor-Davidson Resilience Scale (CD-RISC; [136]), State-Trait Anxiety Inventory (STAI; [114]), Cognitive Emotion Regulation Questionnaire (CERQ; [198]), Difficulties in Emotion Regulation Scale (DERS; [199]), Brief Resilience Scale (BRS; [137]), Prosocialness Scale for Adults (PSA; [200]) Multidimensional Assessment of Interoceptive Awareness (MAIA; [201]), Fear of Compassion Scale (FoC; [202]), Sussex-Oxford Compassion Scales (SOCS; [203]), State Self-Compassion Scale–Long Form (S-SCS; [204]), Interpersonal Reactivity Index (IRI; [205]) and Toronto Alexithymia Scale (TAS-20; [189]). The following COVID-19 related self-generated questions will also be assessed: belonging to COVID-19 biological risk group, belonging to COVID-19 professional risk group, positive test result for COVID-19, presence of COVID-19 symptoms, hospitalization due to COVID-19 and the duration of hospitalization, the history of or current presence of long-covid symptoms, status of COVID-19 vaccination (received none, first or both doses), perception of benefits of COVID-19 vaccination (in case of one or two doses received), willingness to receive COVID-19 vaccination (in case of no vaccine dose received), and impact of COVID-19 related restrictions and limitations. Participants will also answer questions regarding their smoking behavior, alcohol consumption behavior (using AUDIT-C; [206]), current pregnancy (if any), use of hormonal medication, presence of endocrine disorders, oral contraceptive use, and Body Mass Index (BMI). The questionnaires will be completed using a mobile and web app.

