#### Weekly assessments during intervention

We will assess weekly changes in mechanistic variables of interest over the period of 10 weeks of intervention using the mobile or web app designed for the study. Participants will once a week complete CERQ, Perceived Stress Scale– 4-item version (PSS-4), FoC Scale (only following subscales will be assessed: Fear of Expressing Compassion for Others and Fear of Expressing Kindness and Compassion Towards Oneself), S-SCS (only following subscales will be assessed: Self-Kindness and Common Humanity), Mindfulness scale (CAMS-R [211] or FFMQ [212]), MAIA (only following subscales will be assessed: Self-Regulation and Body Listening), IRI (only subscale Personal Distress will be assessed), Penn State Worry Questionnaire-3 [213], Cognitive Control and Flexibility Questionnaire (CCFQ; [214]), Acceptance and Action Questionnaire (AAQ-II; [215]), Brief COPE, Inclusion of Other in the Self Scale (IOS Scale; [216]), stress assessment and stressor appraisal questions [209], and three self-generated questions on frequency and quality of social interaction and empathic listening.

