#### Daily assessment pre and post daily intervention exercise

We will assess daily changes in mechanistic variables of interest over the period of 10 weeks of intervention using the mobile or web app designed for the study. Participants will be asked to evaluate their feeling of engagement with the exercise on a daily basis after the training session. Questions pre and post daily exercise sessions that will be presented alternately every other day include affective state (Affect Grid), valence, temporality and social orientation of thoughts (Cube of Thoughts), feeling of connectedness to partner (IOS), level of interoception (awareness of bodily sensations), and perceived loneliness. Level of personal detail shared (personal disclosure) will only be assessed after the Affect Dyad exercise in the socio-emotional intervention.

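### Daily loneliness is set up as a mediator of the fall in loneliness, so the planned criterion can show mediation where there is no mechanism

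*Protocol article*

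**What the plan says.** All places are in the protocol article.

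- **Outcome.** The pre-post questionnaires include "Perceived Stress Scale-10 (PSS-10; [196]), UCLA Loneliness Scale [197"; the UCLA scale is the questionnaire measure of loneliness.
- **Hypothesis.** The section Loneliness and social connectedness states: "We also expect changes in thought patterns [105], affective states [106] and daily loneliness [107] before and after the dyad". After listing further weekly variables and predicting that socio-emotional training will do better than mindfulness on loneliness, it ends: "We will assess changes in the above postulated mechanistic variables suggested to mediate the reduction in loneliness in the socio-emotional training". It makes no exception for daily loneliness.
- **Daily battery.** The section on daily assessments introduces its items as mechanistic variables. The list includes "level of interoception (awareness of bodily sensations), and perceived loneliness".
- **Analysis.** The Statistical analysis plan fits growth curves to daily and weekly mediators and regresses the slopes on training group (path a). It relates the slopes to latent change in the primary outcomes (path b). It measures mediation by comparing the training effect with and without control for the mediator (c' against c).
- **Control group.** The Procedure section says that the retest control group completes no daily or weekly assessments in the first intervention period.
- **Stress.** The Stress section names "a decrease in loneliness [97, 98] and changes in current thought patterns [99, 100] and affective states [101" among the mechanisms expected to reduce stress. The weekly battery opens with "Participants will once a week complete CERQ, Perceived Stress Scale– 4-item version (PSS-4".

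**The concern.** A mediator should be a different thing from the outcome, something the training changes and which then changes the outcome. A daily loneliness rating and the UCLA scale are different instruments with different time frames, but they measure the same construct over the same ten weeks. Controlling one for the other removes part of the training effect because the outcome is being adjusted for another reading of itself. Comparing c with c' cannot tell that apart from a causal pathway.

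This bears on a stated hypothesis. The plan predicts a difference between the two trainings on loneliness, which is the condition under which the artefact appears. It also expects the trainings to work through distinct mechanisms. A same-construct pair would tend to look like one of the strongest of them.

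**Working it through.** **The plan's own figures.** The article gives no mediated share to reproduce. Its one design figure is the total of 297. With f = 0.10, correlation 0.39, three groups and two occasions, the noncentrality is 297 × 0.01 × 2 / (1 − 0.39) = 9.74 on 2 and 294 degrees of freedom. Power is 0.8002, so the figure reproduces. This point does not affect it.

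**Inputs.** The criterion (c against c') comes from Mediation analysis, and the slope-to-change path from the subsection on associations between changes. The reliability of the daily slope is not in the documents. It is an assumption, shown over a range.

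**A model with no mechanism.** Let X be training arm (socio-emotional or mindfulness) and T a person's true change in loneliness:

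- T = cX + u
- UCLA change: Y = T + e2
- daily loneliness slope: M = T + e1

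Nothing runs from M to Y. They are two readings of T. Then:

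- a = c
- b = Var(u) / (Var(u) + Var(e1)) = R, the within-arm reliability of M
- c' = c − ab = c(1 − R)
- mediated share = (c − c') / c = R

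A different scale for the daily item changes nothing. If M is multiplied by k, then a = kc and b = R/k, so ab is still Rc.

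**Numerical check.** Simulation with c in units of the SD of u, and equal reliability for both measures:

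| Assumed R | c, c' (1,000,000 per arm, c set to 0.5) | Share | Share, 100 per arm, c = 0.5 | Share, 100 per arm, c = 0.2 |
|---|---|---|---|---|
| 0.30 | 0.503, 0.352 | 30% | 30% | 30% |
| 0.50 | 0.498, 0.249 | 50% | 50% | 51% |
| 0.70 | 0.501, 0.151 | 70% | 69% | 70% |
| 0.90 | 0.499, 0.050 | 90% | 91% | 91% |

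The share does not depend on the size of the effect. The columns for 100 per arm are ratios of averages over 1,000 simulated trials. They show where the estimate centres, not how steady it is in one trial.

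**If the overlap is only partial.** In general, share = r × (training effect on the slope in SDs) / (training effect on the outcome in SDs), where r is the within-arm correlation of slope and outcome change. If the training moves the daily slope half as far as the UCLA change in SD units, r = 0.3 gives 0.3 × 0.5 = 15% and r = 0.9 gives 0.9 × 0.5 = 45%. The share is smaller, but still above zero with no mechanism.

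**Which contrast.** The waitlist group has no daily slope in the first period, so path a and the mediated share can be estimated only between the two active arms.

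**The case against.** The best counter-argument is about the wording. The loneliness section opens by saying that loneliness will be followed both pre-post and by momentary assessment, which treats the momentary rating as an outcome. Daily loneliness then appears as an expected change. The closing sentence could be meant to cover only connectedness, disclosure, social interaction, belonging, common humanity, fear of compassion and support. Where the text plainly calls loneliness a mediator, it does so for stress, which is a legitimate use. The article also refers to a preregistration for the detailed hypotheses, and the plan already models pre-session and post-session variables as secondary outcomes.

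The narrow reading is possible but not the natural one. The closing sentence points back to everything above it, and the daily section puts perceived loneliness in the mechanistic set. Even on the narrow reading, one variable has two roles and the text does not say which applies in the loneliness model.

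A second objection stands in full: the size of the share is assumed. No figure in the documents says how closely a momentary rating follows the UCLA scale, and a small difference between two active arms would make the ratio unstable.

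**Conclusion.** The point holds for loneliness. As written, the plan makes daily loneliness a mediator of the reduction in loneliness, and its criterion would report mediation from shared measurement alone. If the two measures share their change and the arms differ, a share above zero is built in. It is 30% to 90% for assumed reliabilities of 0.3 to 0.9, and lower if the overlap is partial. The actual size cannot be known from the documents, and it refers to socio-emotional against mindfulness training only.

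A reader might go further in three ways that the text does not support:

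- **PSS-4 as mediator of the PSS-10.** The PSS-4 is in the weekly battery, introduced with "We will assess weekly changes in mechanistic variables of interest over the period of 10 weeks of intervention", but the Stress section does not name it as a mediator and no section pairs it with the PSS-10. Since it is a shorter version of the same scale, ruling the pair out is a sensible precaution and no more.
- **The other repeated scales** (CERQ, FoC, S-SCS, MAIA, IRI). Being in both batteries does not make a scale a mediator of itself. The plan never says that every mediator is crossed with every outcome, and it mostly uses these constructs to explain other ones.
- **A mediator identical with the outcome, so that a large share is certain.** A momentary rating and the UCLA scale share a construct and are not the same measure. The size of the share does not follow by construction.

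**What to change.** In Loneliness and social connectedness, and in the Statistical analysis plan subsections on mediator change, associations and mediation:

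1. State that daily loneliness is not a mediator of loneliness. Report it as an outcome trajectory during training, socio-emotional against mindfulness. The growth model conditional on training arm, already planned, provides this.
2. Keep daily loneliness as a mediator of other outcomes, such as stress.
3. As a precaution, add a sentence that the weekly PSS-4 is not used as a mediator of the PSS-10.

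The cost is wording in the analysis plan and one or two mediation results not reported. Data collection and sample size are unchanged.

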#### Mental health: Depressive and anxious symptoms

Another area of focus for this phase of the study is to assess intervention-related effects on major mental health outcomes. Therefore, we will examine pre-post changes in depressive and anxious symptoms in our sample using Beck Depression Inventory-II (BDI-II; [113]) and State-Trait Anxiety Inventory (STAI; [114]). Previous studies using MBSR and MBCT have shown significant reductions in these symptoms [115, 116]. Similarly, studies employing socioemotional interventions have shown reductions in symptoms of depression and anxiety [43, 117]. Although the mechanisms through which these changes occur are not fully clear, there is preliminary evidence suggesting the key role of changes in emotion regulation strategies used [72, 118, 119]. Therefore, in the present study, we expect an intervention-related decline in depressive and anxious symptoms, compared to retest control group, owing to a change in use of emotion regulation strategies such as increase in acceptance and decrease in rumination [72, 73, 120]. Further, we will also examine the mechanistic role of other factors that are purported to be involved in the onset and maintenance of depressive and anxious symptoms, namely cognitive control over emotions [121, 122], psychological flexibility [123, 124] social support [125], mindfulness [73, 120], and worry [126]. Furthermore, daily fluctuations in affective states and thought patterns will be evaluated as potential mediators of intervention-related changes in depression and anxiety. Daily fluctuations in affective states will be assessed using the ‘Affect Grid’ [127] which measures both the current valence and the affective arousal. Further, we will use ‘Cube of Thoughts’ [100] to assess the intervention-related changes in valence (positive or negative), temporality (past- or future-oriented) and content (self- or other-related) of thoughts. Previous research has linked fluctuations in affect and thought patterns to be associated with depressive and anxious symptoms [128–131]. We will examine changes in mediators using the daily and weekly EMA approaches, employing a variety of validated questionnaires (please see Measures section). Lastly, we will also examine changes in key mechanisms of negative attention bias and negative interpretation bias that underlie the onset and maintenance of depressive and anxious symptoms [132–134]. Both attention bias and interpretation bias will be assessed using the Mouse-Contingent Scrambled Sentences Task [135].

In the current study, we expect both mindfulness-based and socio-emotional interventions to produce significant changes in depression and anxiety symptoms. However, we expect these changes to function through distinct mechanisms, as the type of practice should likely dictate changes in specific mechanistic domains. We expect differential changes in these mediators depending upon the intervention group, which is expected to influence the magnitude of change in depressive and anxious symptoms in the two intervention groups. For example, while both mindfulness-based and compassion-based programs have been shown to reduce the use of rumination as emotion regulation strategy [117], only compassion-based interventions lead to an increase in use of acceptance as emotion regulation strategy [72]. Therefore, we expect differential effects of the different types of interventions on changes in depression and anxiety symptoms.

#### Psychological resilience

We will also examine pre-post changes in psychological resilience in the 3 groups using the Connor-Davidson Resilience Scale (CD-RISC; [136]) and the Brief Resilience Scale (BRS; [137]). In the current study, we conceptualize psychological resilience both as the ability to adapt to stressful situations and also as the ability to bounce back after a stressor [28, 137, 138]. Previous studies have shown that resilience improves upon undergoing mindfulness-based interventions [62]. A key mechanism underlying this change is purported to be psychological flexibility [123, 139]. Further, socio-emotional interventions have also shown success in enhancing stress adaptation, in terms of stress reactivity, in the face of social stressors [76]. However, the effects on the ability to bounce back after a stressor, in terms of the degree of recovery from stress, remain unclear along with the mechanism underlying these changes. Positive coping styles, use of adaptive emotion regulation strategies, and psychological flexibility are purported to be some of the core mechanisms underlying resilience [140]. Further, other mechanisms proposed to be underlying resilience processes will also be investigated, namely cognitive control over emotions [141], self-compassion [142, 143], mindfulness [144], and increase in use of adaptive and decrease in use of maladaptive emotion regulation strategies [145]. Therefore, in the current study we will examine whether the change in coping strategies, such as enhanced social support, greater use of adaptive emotion regulation techniques such as acceptance, decreased use of maladaptive emotion regulations strategies such as rumination and worry, greater mindfulness and self-compassion, greater cognitive control over emotions, and improved psychological flexibility will predict pre-post changes in resilience in our intervention groups, compared to the retest control group. Furthermore, daily fluctuations in affective states and thought patterns will also be evaluated as potential mediators of intervention-related changes in resilience [146]. We will examine changes in mediators using the daily and weekly EMA approaches, employing a variety of validated questionnaires (please see Measures section). In the current study, we expect both mindfulness-based and socio-emotional interventions to produce to significant changes in resilience. However, we will investigate whether different interventions distinctly impact the two components of resilience, namely the ability to adapt to stressful situations and the ability to bounce back. Further, we again expect these changes in resilience to function through distinct mechanisms, as the type of practice will likely dictate changes in specific mechanistic domains. We expect differential changes in use of coping and emotion regulation strategies and changes in psychological flexibility depending upon the intervention group, which is expected to influence the magnitude of change in resilience in the two intervention groups. For example, while both mindfulness-based and compassion-based programs, such as MBCT and CFT, have been shown to enhance mindfulness, the effect sizes are larger for mindfulness-based intervention [117]. However, care and compassion-based socio-emotional intervention will perhaps lead to enhanced use of coping strategies such as acceptance and obtaining social support, which will likely impact distinct components of resilience. Therefore, we expect differential effects of the different types of interventions on changes in resilience.
